### Trial training

Trial coordinators will meet virtually with delegated NHS research teams via video call at each proposed RAPSODI site in order to discuss the study and provide training of specific processes. Sites will also be provided with guidance on how to collect the ROM and Strength measures using the equipment provided by the Sponsor. Trial coordinators will continue to liaise with sites during recruitment to ensure adherence to the protocol, completion of data collection and training of new staff members, as applicable.

#### Interventions

For both interventions, we will only include commercially available, off-the-shelf implants. We define ‘off the shelf’ as not designed or bespoke but taken from existing stock or supplies. Some hospitals will use fluoroscopic imaging during surgery, as part of their standard practice.

To reflect the pragmatic design of this trial, a required level of experience of the operating surgeon will not be defined, although all surgeons performing TSR for patients within the trial will be required to be familiar with the techniques and equipment that they are using. Data will be collected on the grade and experience of the primary and secondary surgeons through the NJR minimum data set.

The treatment of the rotator cuff during the surgical approach and repair on completion of the surgery will be recorded but will be left to the discretion of the operating surgeon. The surgical approach may include a deltopectoral or deltoid splitting approach and will depend on local practice at recruiting sites. This will not be mandated in the protocol in keeping with the pragmatic design but will be recorded. There may be some patients who are initially randomised to aTSR whose rotator cuff is deemed unsuitable at surgery and thus receive rTSR instead. These patients will be followed up under intention-to-treat and the incidence of these crossovers will be monitored throughout. Figure 2 illustrates the two types of TSR that are described below.

**Figure 2 F2:**
[figure not shown]
Diagram of a total shoulder (anatomic) replacement (left) and a reverse shoulder replacement (right).

##### Anatomical total shoulder replacement

The aTSR is a conventional TSR which mimics the natural structure of the shoulder joint. The choice of implant will depend on local practice at recruiting sites but will include any anatomical shoulder implant from any manufacturer licensed for use in the UK. We will record and report the implants used. Due to its close relationship to normal shoulder anatomy, aTSR has the potential to provide patients with a return to a normal range of shoulder function; however, there is an associated risk of future revision due to failure of the rotator cuff.

##### Reverse total shoulder replacement

For the rTSR, the arrangement of the ball and socket component parts is reversed making use of the deltoid muscle for movement of the arm: it does not rely on an intact or functioning rotator cuff. The choice of implant will depend on local practice at recruiting sites but will include any reverse shoulder implant from any manufacturer licensed for use in the UK implanted using techniques consistent with manufacturer instructions. We will record and report the implants used.

### Post-operative care

Participants in both arms of the trial will be offered usual post-operative care including physiotherapy which can be delivered in person, remotely or using a hybrid model (as per usual care at participating sites). We will provide physiotherapists with the slides from a presentation given by a co-author at the 2022 British Elbow and Shoulder Society about the best current available evidence on rehabilitation after TSR. The timing and frequency of the physiotherapy will follow routine practice at participating sites. Where possible within the governance in place for each site, we will collect data including the content and number of physiotherapy sessions. We will also collect and summarise documents from participating sites that describe their typical post-operative rehabilitation protocols for participants having TSRs including exercise leaflets or templates.

### Outcomes

There is no consensus on the optimal outcome measures in shoulder arthroplasty, although Outcome Measures in Rheumatology Clinical Trials (OMERACT) has recommended four mandatory domains for trials of shoulder disorders: pain, function, global effect and adverse events.^13^ In choosing the primary outcome measure for this trial, we have followed the guidance of the Difference ELicitation in TriAls (DELTA) group and DELTA-2.^14^ The SPADI is very reliable, has low floor and ceiling effects, is valid for use in shoulder arthroplasty research and, as it is highly sensitive to change, it best enables us to answer the question of superiority of rTSR over aTSR in the two key domains identified by both the Patient and Public Involvement (PPI) group and OMERACT, namely pain and function.^15^ There is also a strong correlation between SPADI score and ROM.^16^ The Oxford Shoulder Score (OSS) is included as a secondary outcome to enable comparison of the trial population with the NJR dataset to explore external validity. The NJR has previously evidenced ceiling effects of the OSS in shoulder arthroplasty and lower responsiveness to change, making it unsuitable as the primary outcome instrument.^17^ NICE has recommended the primary outcome should be collected at 24 months post-surgery.^10^

#### Primary outcome

The primary outcome is the total pain and disability score measured using the SPADI at 24 months. The 13-item SPADI is a validated and sensitive instrument for use in TSR that assesses two domains: pain (five items) and functional activities (eight items) on numerical rating scales.^15 18^ The total score ranges from 0 to 100 where 0 indicates no shoulder pain or disability and 100 indicates worst possible shoulder pain or disability.

#### Secondary outcomes

Combined pain and disability score: measured via the combined SPADI score at 3, 6, 12 and 18 months, and over 24 months.Individual pain and disability scores: measured via the subscale scores of the SPADI at 3, 6, 12, 18 and 24 months, and over 24 months.Pain and function: measured via the OSS, which is a 12-item patient-reported outcome measure of shoulder pain and function with five response categories and overall scale ranging from 0 (worst) to 48 (best).^19^ The OSS will be collected at 3, 6, 12 and 24 months.Global perceived effect: patient opinion about the change in their shoulder since the start of the trial will be assessed at 24 months via the question “Compared with just before the operation for your shoulder replacement at the start of the study, how would you say that your shoulder is now?”. Responses will be on a 5-point Likert scale with the following options: much improved, improved, same, worse and much worse.^20^Health-related quality of life: measured at 3, 6, 12 and 24 months via the EQ-5D-5L, a validated measure of health-related quality of life in terms of five dimensions (mobility, ability to self-care, ability to undertake usual activities, pain and discomfort, anxiety and depression) each with five levels of severity.^21^ The EQ-5D-5L will be used to calculate quality-adjusted life years (QALYs) according to NICE best practice guidance at the time of the analysis.ROM: The range of shoulder flexion, abduction, internal and external rotation will be assessed by a suitably trained blinded assessor at 24 months using a hand-held goniometer following trial specific instructions and recorded as continuous measurements except for internal rotation that will be assessed according to the position of the thumb to the spine.^22^Strength of shoulder: Shoulder strength will be measured at 24 months using a spring balance as described for the Constant Murley Score by a suitably trained blinded assessor.^22^ This will be done for both shoulders and repeated three times and will only be completed if the arm can be elevated to 90 degrees (abduction). Neither strength nor ROM will be collected during the interim follow-up timepoints given the need for in-person measurements by a trained team member. Both ROM and strength measurements will be collected only at baseline and at 24 months.Complications: Expected complications related to the affected shoulder will be recorded and will include (but are not limited to) deep and superficial wound infection (using Centers for Disease Control and Prevention definition),^23^ re-hospitalisation, and implant, nerve and skin problems. These complications will be recorded at 3, 6, 12 and 24 months. Complications specific to the arthroplasty implant (ie, glenoid loosening (keeled and pegged), scapula notching and lucency of the humeral stem)^24^,^26^ will be reviewed by the local surgeon using post-operative radiographs (typically anteroposterior and axial views) and 2 year radiographs (typically anteroposterior and axial views) or the most recent radiographs if not available at 2 years. This assessment will be performed using routinely taken radiographs and where feasible by a local surgeon who did not operate on the participant. Depending on the availability of funding, these radiographs will be pseudonymised of personal data and collected for central review independent of the surgeons at the local hospital.Re-operations: An operation to correct the complications of a previous operation due to, for example, an infection or dislocation. Re-operations will be recorded at 3, 6, 12 and 24 months.Revision and mortality: Rates of implant revision and patient mortality over the 24-month follow-up will be collected from hospital and the NJR records to identify patients in whom revision was undertaken elsewhere or death that is not recorded in the hospital records. The NJR definition of a revision will be used, which is any operation where one or more components are added to, removed or modified in a joint replacement or if a Debridement And Implant Retention with or without modular exchange is performed.^27^Resource use: Data on healthcare resource use will be collected to inform the economic evaluation (eg, length of hospital stay, re-hospitalisation, physiotherapy). Data will also be recorded about use of private care, days lost to work and normal activities. These data will be collected from participants and hospital records at 3, 6, 12 and 24 months.

##### Baseline data

The SPADI, OSS, EQ-5D-5L, ROM and shoulder strength will be collected at baseline by research teams at each site. Other validated measures at baseline will be a patient-reported 5-item frailty scale,^28^,^30^ a five-stage grading of muscular fatty degeneration,^31^ a co-morbidity index,^32^ an assessment of glenoid erosion via Walch’s classification^33^ and socio-demographic characteristics of participants. Ideally, shoulder ROM and strength will be collected before randomisation, along with other baseline data. However, in some cases, a blinded assessor may collect these data after randomisation (with the participant also blinded) as randomisation should occur ideally 2 weeks before surgery to allow for surgical planning and the patient may not be present at the time of randomisation.

### Participant timeline

Figure 3 illustrates the overall schedule and flow of trial participants through the trial based on the recommended figure in the SPIRIT, from initial eligibility screening, consent, baseline data collection and randomisation, treatment delivery and follow-up data collection timepoints.

**Figure 3 F3:**
[figure not shown]
RAPSODI-UK trial assessment schedule. ROM, range of movement; SPADI, Shoulder Pain and Disability Index. ^1^Baseline assessments will be prior to randomisation except for baseline Range of Movement and Strength which may be collected, when necessary, after randomisation by an independent blinded assessor. ^2^This includes radiographs (typically anteroposterior and axial) to confirm osteoarthritis; CT or other imaging to assess glenoid erosion; and CT, MRI or US to assess the rotator cuff. ^3^Assessment of cuff integrity in theatre before operating and the possible use of fluoroscopy during surgery. ^4^This includes an assessment of implant problems using post-operative radiographs and radiographs at 24 months or earlier if not available. The radiographs will typically be anteroposterior and axial.

### Sample size

The primary outcome is the total SPADI score at 24 months. As our trial compares two active treatments, we expect a relatively small difference in SPADI score between groups at 24 months, so our target difference between the rTSR and aTSR groups is eight points (the smallest published, validated difference classed as clinically important).^34^ We also conservatively assumed a group SD of 25 points, based on three non-randomised studies.^35^,^37^ We plan to use a linear mixed-effects model in the primary outcome analysis, but due to a paucity of data in the literature to inform our between-measurement correlations, we instead calculate the sample size estimate based on an ANCOVA (‘baseline-as-a-covariate’) model.

Assuming a baseline/24-month SPADI score correlation of 0.35,^38^ 182 participants per group (364 total) are required to give 90% power to detect a difference of at least eight points (SD 25) between aTSR and rTSR, and a 5% significance level. Allowing for 15% loss to follow-up at 24 months,^39^ we aim to randomise a total of 430 participants.

The OSS is our key secondary outcome measure allowing direct comparison of the trial population to those in the NJR in order to explore external validity of the trial sample. Assuming a between-group difference of 2.7 points on the OSS, an expected SD of 8.80, and a baseline correlation of 0.35, the sample size of 430 would achieve 87.5% power using a similar ANCOVA analysis method and the same underlying assumptions.

### Data collection

Data will be collected from participants at baseline, 3-, 6-, 12-, 18- and 24-months post-randomisation. There will be a secondary outcome endpoint of 18-month follow-up to collect the SPADI only to try to help maintain trial engagement and reduce missing data of the primary outcome. Baseline data will be collected with participants at recruiting sites by a delegated member of staff, for example, research nurses. Follow-up data collection of the primary outcome and most secondary outcomes will be by postal questionnaire with supplemental telephone/video conference follow-up for non-responders or collected in clinic when attending at these timepoints as part of their routine care. Delegated research staff will also collect data from hospital records at 3, 6, 12 and 24 months. This includes a local assessment of routine post-operative radiographs and those routinely taken at 24 months (or earlier if not routinely available at this timepoint) to assess complications specific to the arthroplasty implant. Final follow-up data collection will include an outpatient clinic attendance at 24 months to assess shoulder ROM and strength by a blinded assessor. All reporting of data collection will be undertaken in line with the CONSORT statement.^12^

To minimise attrition, we will use multiple methods to maintain contact with participants, including full contact details (postal address, mobile phone number and email address if available). For postal data collections, two reminders will be sent to non-responding participants (at 2 and 4 weeks past the due date), with a final attempt to obtain data 6 weeks post-due date. Newsletters will be circulated to participants during the trial to keep them informed and engaged.^40^ Given that the 24-month follow-up clinic is not a routine appointment at all participating hospitals, all trial participants will receive a £20 gift voucher for attending the clinic and as a thank you for completing their follow-up questionnaires.

#### Data management

The participant questionnaires and hospital Case Report Forms (CRFs) will be designed using TeleForm software.^41^ The data collected by trial participants and sites using paper CRFs will be mailed (original paper CRFs) to York Trials Unit to be entered/scanned using TeleForm. When necessary, a site can securely return the CRF electronically. Participant questionnaires will be checked for missing data on receipt by York Trials Unit. In these instances, participants will be called to collect any missing primary outcome data and other missing data as feasible. Data collected via telephone or video call will be collected onto paper CRFs. As a duty of care, questionnaires will be checked immediately for anything that indicates that the participant could be at risk of harm. Where this occurs, the hospital team will be notified via email. To maximise data quality, key variables in the hospital CRFs will be reviewed by a York Trials Unit research data administrator for completion and accuracy, who will resolve any queries with staff at the relevant site. Following these initial checks, all CRFs will undergo a scanning process within TeleForm software, followed by second checking and validation against predetermined rules. A York Trials Unit data management system will be used to monitor CRF returns.

All data will be stored and transferred following York Trials Unit standard operating procedures. The staff involved in the trial (both at the sites and York Trials Unit) will receive training on data protection. The staff will be monitored to ensure compliance with privacy standards. Each site will hold data according to the General Data Protection Regulation as implemented in the Data Protection Act 2018.^42^ Essential trial documentation will be kept within the Trial Master File and Investigator Site Files. The Sponsor will ensure that this documentation is retained for a minimum of 5 years after the conclusion of the trial. All study-related information will be stored securely in the coordinating centre at the University of York. All electronic records will be stored on a password-protected server.

The Data Monitoring and Ethics Committee (DMEC) will be the only body to have access to the unblinded comparative data from the trial. The role of its members is to monitor these data and make any recommendations to the Trial Steering Committee (TSC) on whether there are any ethical or safety reasons why the trial should not continue. The TSC will provide overall supervision for the trial on behalf of the Sponsor and Funder.

#### Embedded Study Within A Trial (SWAT)

A SWAT will be conducted around participant retention with an embedded 1:1 RCT to investigate the impact of a newsletter sent 6 weeks prior to each of the 18- and 24-month follow-ups on completed SPADI follow-up rates at these timepoints (primary outcome 24-month SPADI completion), as a replication of registered SWAT 28.^40^

#### National joint registry linkage

Rates of implant revision and patient mortality at 24 months will be collected from hospitals and the NJR records to identify participants in whom revision was undertaken elsewhere (to the recruiting site) or death not recorded in the hospital records. An expression of interest has been registered with the NJR of England, Wales and Northern Ireland to embed the trial for collection of this data. Separate funding will be sought to investigate survival outcomes up to 5, 10 and 15 years in our trial participants.

In addition to the OSS, other characteristics of our trial population will be compared with the NJR cohort, such as age and gender. Participants will be asked if they agree to consent to complete questionnaires at future timepoints beyond the 24-month follow-up (subject to the progress of this trial and future funding) to further investigate long term outcomes.

### Statistical methods

Statistical analyses will be detailed in full in a Statistical Analysis Plan agreed by the independent DMEC prior to the end of data collection and are described in brief below.

Statistical analyses will be on an intention to treat (ITT) basis, with participants analysed in the groups to which they were randomised. Between-group treatment differences will be reported in the form of point estimates with 95% CIs and p values. Statistical significance will be declared at the 5% level, and analyses will be conducted in the latest available version of Stata or similar statistical software.

Baseline characteristics will be reported descriptively overall and by treatment group. Continuous data will be summarised as means, SD, medians and ranges as applicable, and categorical data as frequencies and percentages. All trial outcomes will be reported descriptively by group at all time points at which they were collected.

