#### Secondary outcomes

The between-group differences for total SPADI score at 3-, 6-, 12- and 18-months, and over 24 months will also be extracted from the primary analysis model as secondary outcomes. The other secondary continuous outcomes (eg, SPADI pain and function subscale scores, OSS) will be analysed using an identical mixed-effects model with the same covariates and covariance structure. While also a continuous secondary outcome, the EQ-5D-5L will exclusively be used in the health economic evaluation.

ROM and strength are collected at two timepoints (baseline and 24 months). The 24-month outcomes for these measures will be compared via a mixed-effects linear regression model with intervention group as the predictor variable, as well as age, gender and baseline value of the outcome, and site as a random effect.

The ordinal outcome of the global perceived effect outcome at 24 months will be analysed using mixed-effects ordinal logistic regression, adjusting for age, gender and baseline combined SPADI score, with site as a random effect. Time-to-event outcomes (time to revision/re-operation/death) will be explored by comparing restricted mean survival times between intervention groups. Safety outcomes (adverse event rate, complication rate and types of complication) will be summarised across all timepoints at which they are collected.

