#### Additional analyses

There is the potential for participants in this trial not to receive their allocated intervention (eg, surgery not performed, or they cross over from one treatment arm to the other). A complier average causal effect (CACE) analysis will be carried out at the 24-month time-point to account for this. Compliers are defined as participants who received their allocated TSR. The CACE analysis will be implemented using a two-stage least squares instrumental variable approach with randomised treatment assignment as the instrument variable and the received allocated TSR as the exogenous variable.^45^ The linear regression model will control for age, gender and baseline total SPADI score.

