### Adverse event reporting and harms

Adverse events (AEs) will be defined as any untoward medical occurrence in a trial participant to whom a treatment has been administered, and which does not necessarily have a causal relationship with the treatment. Only medical occurrences related to treatment for the shoulder condition that are ‘unexpected’ and up until the 24-month follow-up will be classified as events when non-serious. This is because ‘expected’ events are well known complications for the two routine treatment options which the specialist clinical care teams will be experienced in managing.

Serious adverse events (SAEs) will be defined as any untoward medical occurrence that:

Results in death.Is life-threatening (that is, it places the participant, in the view of the Investigator, at immediate risk of death).Requires hospitalisation or prolongation of existing inpatients’ hospitalisation (unplanned refers to emergency hospitalisations resulting in an inpatient stay; prolonged hospitalisation is deemed to be where a patient’s stay is longer than expected).Results in persistent or significant disability or incapacity.Any other important medical condition which, although not included in the above, may require medical or surgical intervention to prevent one of the outcomes listed.

SAEs that may be expected as part of the surgical interventions and that do not need to be reported to the main REC include: complications of anaesthesia or surgery (eg, wound complications, infection (superficial and deep), damage to a nerve or blood vessel and thromboembolic events), skin problems, implant problems (eg, fracture, rotator cuff tear and instability) and secondary operations for or to manage instability, infection, fracture, non-union or for symptoms related to the prosthesis.

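### Complications, re-operations and revisions are reported by randomised group only, although crossover from aTSR to rTSR is foreseen and some tracked complications belong to the implant

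*Protocol article*

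**What the plan says.** The general rule is in the protocol article, Statistical methods: "Statistical analyses will be on an intention to treat (ITT) basis, with participants analysed in the groups to which they were randomised". The same section adds: "All trial outcomes will be reported descriptively by group at all time points at which they were collected".

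Under the statistical Secondary outcomes heading, safety has one sentence: "Safety outcomes (adverse event rate, complication rate and types of complication) will be summarised across all timepoints at which they are collected". Revision, re-operation and death are handled next to it: "Time-to-event outcomes (time to revision/re-operation/death) will be explored by comparing restricted mean survival times between intervention groups". Neither sentence names a safety population, a denominator or a grouping by implant received.

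The Interventions section foresees conversion at surgery: "There may be some patients who are initially randomised to aTSR whose rotator cuff is deemed unsuitable at surgery and thus receive rTSR instead". It keeps these participants under intention to treat and says that their incidence will be monitored. Additional analyses also allows for "surgery not performed, or they cross over from one treatment arm to the other", and answers with a complier average causal effect (CACE) analysis at 24 months whose linear model adjusts for baseline total SPADI.

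The Secondary outcomes list under Outcomes includes a set of complications specific to the implant: glenoid loosening, scapula notching and lucency of the humeral stem. Background and rationale reports that, in the cited meta-analysis of retrospective studies, notching was seen only with rTSR and glenoid loosening was more common with aTSR.

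**The concern.** Some of the recorded harms depend on which implant is in the shoulder. A participant allocated to aTSR but given an rTSR can develop notching, and under the stated rule that event appears in the aTSR column. The same shoulder has no anatomic glenoid component, yet it stays among those counted when anatomic glenoid loosening is reported for the aTSR arm.

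Crossover is no remote possibility in this trial. It is listed among the limitations, and estimating it is an objective of the internal pilot. For effectiveness, the plan recognises that the treatment received may differ from the allocation and adds the CACE analysis. It states nothing comparable for harms.

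A reader who wants the risk attached to each implant, or who wants to compare the trial with the registry rates per 100 prosthesis-years quoted in Background and rationale, could not do so directly from tables by allocation alone.

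**Working it through.** **Inputs from the document.** Total randomised 430, allocation 1:1, so 430 / 2 = 215 per arm. The point disputes no stated figure. As context, the sample size reproduces. With SD 25 x sqrt(1 - 0.35^2) = 23.42, difference 8, two-sided 5% (assumed two-sided) and 90% power, the normal approximation gives 181 per group against 182 stated, and 182 gives 90.3% power. 364 / 0.85 rounds up to 429 against 430 stated.

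**Inputs assumed, because the document gives none.** Crossover from aTSR to rTSR: c = 2% to 15%. Unoperated share, equal in both arms: u = 0% to 5%. Complication risk by implant received: pa for aTSR, pr for rTSR. Risk is taken as unrelated to crossover. All randomised participants are taken as the denominator, which the document does not say.

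**Model.**
- Risk in the arm allocated to aTSR: (1 - c - u) x pa + c x pr
- Risk in the arm allocated to rTSR: (1 - u) x pr
- Difference: (1 - u) x pr - c x pr - (1 - c - u) x pa = (1 - c - u) x (pr - pa)

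The allocated-group difference is thus the by-implant difference times (1 - c - u).

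| c | u | Share of by-implant difference kept |
|---|---|---|
| 2% | 0% | 98% |
| 5% | 0% | 95% |
| 10% | 5% | 85% |
| 15% | 0% | 85% |
| 15% | 5% | 80% |

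**Example: a complication seen only with rTSR.** Take pr = 10%, pa = 0%, c = 10%, u = 5%.
- aTSR arm: 0.10 x 10% = 1.0%
- rTSR arm: 0.95 x 10% = 9.5%
- Difference by allocation: 8.5 points; by implant received: 10 points

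**Events listed under aTSR that belong to rTSR** (215 x c x pr):
- pr = 10%: 215 x 0.02 x 0.10 = 0.4 and 215 x 0.15 x 0.10 = 3.2
- pr = 20%: 215 x 0.05 x 0.20 = 2.2 and 215 x 0.15 x 0.20 = 6.5

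By implant received, the aTSR count would be zero in each case.

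**Cuff-failure revision.** Background and rationale gives 0.42 (aTSR) and 0.02 (rTSR) per 100 prosthesis-years. With everyone operated and about two prosthesis-years each, the aTSR arm expects 0.42 / 100 x 2 x 215 = 1.8 revisions without crossover. With 10% crossover it expects (0.90 x 0.42 + 0.10 x 0.02) / 100 x 430 = 1.6. The change is small, on very few events.

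**The case against.** The strongest reply is that safety sets and denominators normally belong to the SAP, which is not shown, and that Statistical methods calls itself a brief description. Grouping harms by allocation is also legitimate in a pragmatic trial: conversion to rTSR is a foreseen consequence of being allocated to aTSR, so later events are part of that strategy's record. There are mitigations too. Types of complication are reported, crossover is monitored, implants used are recorded and reported, and nothing confines the DMEC to tables by allocation. Even at 15% crossover and a 20% rTSR-only risk, the arms would show 0.15 x 20% = 3% against 20%, so a gap of that size would not be hidden.

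Much of this stands. Grouping by allocation is not an error and should stay. What remains is that the article states a rule covering all outcomes, and a SAP that followed it literally would group harms by allocation only.

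Three stronger readings are tempting, but the document does not support them.
- A reader might infer that the adverse event definition, "any untoward medical occurrence in a trial participant to whom a treatment has been administered", conflicts with intention to treat. That definition says which events count, not who is analysed. Expected non-serious complications fall outside adverse event reporting and form a separate outcome.
- A reader might infer that unoperated participants are counted as free of implant risk. No denominator for complication rates is stated, so this cannot be concluded.
- A reader might infer that allocation always pulls the implants' risks together. That requires risk to be unrelated to crossover, and participants "whose rotator cuff is deemed unsuitable at surgery and thus receive rTSR instead" may well differ in risk.

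**Conclusion.** The point holds as a modest weakness in a stated rule. As written, complications, re-operations and revisions are reported by randomised group only, and the CACE analysis has no stated counterpart for harms. Any rTSR-specific event in a converted shoulder would then appear under aTSR; that labelling follows from the text and needs no assumed rate.

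The dilution is conditional and small. The allocated-group difference keeps about 98% down to 80% of the by-implant difference for crossover of 2% to 15% and non-operation of 0% to 5%. This rests on assumed rates, on risk unrelated to crossover and on an all-randomised denominator. Crossover alone, with everyone operated, gives 98% down to 85%. The model takes crossover in the direction that Interventions names; Additional analyses does not rule out the reverse, which under the same assumptions would dilute further.

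**What to change.** In the statistical Secondary outcomes section, keep the summary by randomised group as the randomised comparison. Add that complications, re-operations and revisions will also be summarised descriptively by implant received among operated participants, with the denominator stated and time counted from surgery. Give the DMEC both summaries.

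The data are already planned: implants used are recorded under each intervention, complications and re-operations are collected at 3, 6, 12 and 24 months, and revisions come from hospital and registry records. The cost is one extra set of tables. Its drawback is that it is not protected by randomisation, because participants who cross over have poorer cuffs. The table should carry a caution line saying so and should not be read as a causal comparison.
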